### Cost-effectiveness analysis

Cost-effectiveness analyses for the longitudinal and cross-sectional analyses described above will build on a cost-effectiveness model developed for the RHIVA2 trial.^15^ To assess value for money, we will identify the difference in costs and the difference in benefits of implementing the RHIVA2 intervention and we aim to distinguish between two different analyses. First, we will evaluate the cost-effectiveness of the RHIVA2 implementation using the same ‘comparator’ defined in the longitudinal analysis, that is, practices which did not receive the RHIVA2 intervention at any stage will be considered the ‘absence of the intervention’.

Second, we will build a cost-effectiveness comparison between different forms of HIV screening in East London, formally comparing the RHIVA2 implementation (conducted in Hackney) with the sexual health NIS (Tower Hamlets) and usual care (Newham). Once again, all three different approaches will be compared with practices, which did not receive the RHIVA2 intervention at any stage, as these are considered the ‘absence of the intervention’. Given that the same control group of practices in Hackney will serve as reference, this second analysis will formally compare the different approaches from different boroughs, considering no intervention in Hackney as a reference.

Three main cost categories will be explored: (1) the extra start-up cost of RHIVA2 implementation (specifically the cost for RHIVA2 staff time, including follow-up activities; cost of training; cost of training materials and cost of incentives to practices); (2) the extra recurrent cost for performing rapid HIV testing and (3) additional costs associated with reactive rapid HIV test results.

Benefits of the RHIVA2 programme will include health outcomes for patients, specifically deaths averted, secondary HIV infections averted and quality-adjusted life years; these are a function of the uptake of screening and screening positivity, which will be quantified directly by the analyses.

This study is a service evaluation which does not require registration as a trial.

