## Methods and analysis

### Setting

The study will be set in the three East London boroughs of Hackney, Tower Hamlets and Newham. The estimated diagnosed HIV prevalence for these boroughs is 8.1, 6.5 and 6.7 per 1000 adult population, respectively.^21^ We will include all adults aged 16 and above registered with general practices in the three boroughs.

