#### Newham

*Usual care*—no specific borough-wide initiatives were promoted relating to HIV testing in primary care.

The RHIVA2 intervention is based on published clinician behaviour change programmes,^16–18^ and the Tower Hamlets NIS follows Royal College of General Practitioners guidance on establishing general practice federations.^23^ We will report our study in accordance with the STARI reporting guidelines for implementation studies.^24^

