#### Longitudinal analysis of effectiveness of RHIVA2 implementation programme in Hackney

We will compare testing rates using an ITS regression approach with a mixed Poisson model (or negative binomial model if there is overdispersion) to analyse the effect of interventions. Mixed Poisson regression will allow for the clustered nature of the data, that is, allowing each practice to have a different intercept (baseline HIV testing rate). We will also adjust for practice list size as an offset variable in the analysis. Using this approach, it will be possible to examine whether there is a change in level and/or a change in regression slope following the implementation of the intervention.

We will first examine the impact of the RHIVA2 intervention on combined serology and rapid HIV testing rate in practices that received the RHIVA2 implementation (post-trial setting, comparing testing rates preintervention and postintervention). We will repeat this analysis including practices which did not receive the RHIVA2 intervention during the trial or the further implementation phase, to act as a comparator. This will allow comparison of testing rates in practices postimplementation to their preimplementation rates, also adjusting for continuing trends in practices that did not receive the RHIVA2 implementation. We will also repeat the analysis using Newham practices (which received no intervention) as a further comparator.

The date of intervention will be defined as the date of the first RHIVA2 training session. We will conduct similar analysis to the above, with the endpoint of HIV diagnosis, rather than testing.

To assess sustainability, we will model testing rates in practices that received the RHIVA2 intervention during the trial period, considering an interaction term between time postintervention and whether practices were retrained. This will allow an assessment to be made about whether retraining influences the slope postintervention, that is, the sustainability of the RHIVA2 intervention.

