#### Cross-sectional analysis of effectiveness of the RHIVA2 implementation programme in Hackney, a sexual health NIS in Tower Hamlets and usual care in Newham

We will examine the impact of the sexual health NIS on the serology testing rate in all Tower Hamlets practices (comparing testing rates preimplementation and postimplementation). We will repeat this analysis but also including practices in Newham, which received no intervention at any stage, to act as a comparator. The date of intervention will be defined as the date when the sexual health NIS system went live for all practices (April 2011). We will also compare the RHIVA2 implementation in Hackney with the introduction of the sexual health NIS in Tower Hamlets.

We will conduct similar analysis to the above, with the endpoint of HIV diagnosis, rather than testing.

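### The second cost-effectiveness analysis measures Newham usual care and the Tower Hamlets NIS against never-trained Hackney practices, so borough differences can enter the increments

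*Protocol article*

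**What the plan says.** The Cost-effectiveness analysis section plans two comparisons. The first is within Hackney. The second covers the three boroughs, and there "all three different approaches will be compared with practices, which did not receive the RHIVA2 intervention at any stage". The section confirms that these are Hackney practices ("Given that the same control group of practices in Hackney will serve as reference") and concludes that "this second analysis will formally compare the different approaches from different boroughs, considering no intervention in Hackney as a reference". The health benefits are driven by screening: "these are a function of the uptake of screening and screening positivity, which will be quantified directly by the analyses".

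Other sections bear on that choice:

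- **Newham** is described as usual care: "no specific borough-wide initiatives were promoted relating to HIV testing in primary care".
- **The Tower Hamlets effectiveness analysis** compares rates before and after the NIS went live, and then brings in Newham: "We will repeat this analysis but also including practices in Newham, which received no intervention at any stage, to act as a comparator".
- **Setting** gives different burdens of infection: "The estimated diagnosed HIV prevalence for these boroughs is 8.1, 6.5 and 6.7 per 1000 adult population, respectively" (Hackney, Tower Hamlets, Newham in that order).
- **Interventions, Hackney** describes a sexual health Local Enhanced Service (LES) that paid £265 per new diagnosis. From April 2013 this became £7 to £10 per test plus £258 per new diagnosis. The article does not confine those payments to trained practices.

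**The concern.** An increment should compare a strategy with what would have happened in the same population without it. For two of the three strategies the stated reference is in another borough.

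Newham is the clearest case. Nothing was introduced there borough-wide, so it has no start date and no effect to estimate. A cost and benefit increment for Newham over untrained Hackney practices is one no-RHIVA2 condition set against another. Whatever it shows is a difference between places.

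For Tower Hamlets, the effectiveness result and the cost-effectiveness result would answer to different counterfactuals, so the second could not be read as the economic translation of the first.

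The reference is also not free of intervention. The updated LES is listed as a component of the post-trial programme, and untrained Hackney practices may have been paid under it. Newham had no comparable borough-wide scheme.

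The second and third research questions ask for these between-borough comparisons, and commissioners are named as the audience. Differences in prevalence, background uptake, incentives and data extraction could be reported to them as value for money.

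**Working it through.** The article gives no numerical result for this analysis, so there is no figure to reproduce. The check is what the stated reference would show if no intervention had any effect.

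**Inputs from the Setting section.** Diagnosed prevalence per 1000 adults: Hackney 8.1, Tower Hamlets 6.5, Newham 6.7.

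**Assumptions, not in the article.** Positivity is proportional to borough diagnosed prevalence. Never-trained Hackney practices share the borough figure. Background uptake in borough *b* is *r* times that in the reference practices. The article does not give *r*, so it is varied from 0.5 to 1.5.

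**Formula.** Diagnoses = uptake × positivity, so the apparent ratio to the reference is *r* × (prevalence in *b* / 8.1).

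**Step 1, equal uptake (*r* = 1).**
- Newham: 6.7 / 8.1 = 0.827, or 17.3% fewer diagnoses.
- Tower Hamlets: 6.5 / 8.1 = 0.802, or 19.8% fewer.
- Tower Hamlets against Newham: 6.5 / 6.7 = 0.970, or 3.0% fewer.

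**Step 2, varying uptake.** Apparent change against the reference, with no true effect:

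| *r* | Newham | Tower Hamlets |
|---|---|---|
| 0.5 | −58.6% | −59.9% |
| 0.75 | −38.0% | −39.8% |
| 1.0 | −17.3% | −19.8% |
| 1.25 | +3.4% | +0.3% |
| 1.5 | +24.1% | +20.4% |

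The sign changes at *r* = 8.1 / 6.7 = 1.21 for Newham and 8.1 / 6.5 = 1.25 for Tower Hamlets.

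**Step 3, does another reference cure it?** Not if levels are compared. In general (Hackney − reference) − (Tower Hamlets − reference) = Hackney − Tower Hamlets. As ratios at *r* = 1, the Hackney reference gives (8.1/8.1) / (6.5/8.1) = 1.25, and the Newham reference gives (8.1/6.7) / (6.5/6.7) = 1.25. Against Newham, Hackney itself would show 8.1 / 6.7 = 1.21, a spurious 21% gain.

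**Step 4, changes instead of levels.** With no true effect and no drift, each active borough's rate equals its own pre-intervention counterfactual, so its estimated effect is zero whatever its prevalence or uptake. Newham, as the usual-care reference, is zero by definition.

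**The case against.** The strongest reply is that the economic section opens by tying itself to the longitudinal and cross-sectional analyses, and says that uptake and positivity come from them. Those are before-and-after ITS analyses, with practice-specific intercepts described for Hackney. If estimated changes feed the model, baseline differences in testing level cancel for Tower Hamlets. The details may sit in the earlier trial's economic model or a fuller plan, neither of which is shown. This stands in part: the article does not settle whether levels or changes enter. But it does name the reference, twice, and that reference is neither Tower Hamlets' own past nor Newham. Even with changes, differences in trend and prevalence remain, and Newham still has no intervention effect to carry.

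A reader might infer that the ranking is tilted towards Hackney whatever the interventions did. The documents do not support that. Diagnosed prevalence is only a proxy for positivity among those tested, background uptake by borough is not given, and the sign reverses within a plausible-looking range of *r*. Nor can the Hackney reference be blamed for the direct Hackney–Tower Hamlets contrast of levels, since it cancels there (Step 3).

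It is also fair that the article acknowledges limits on comparability between boroughs, and that the same section promises a comparison of RHIVA2 with the NIS and usual care. Acknowledging the limits does not adjust for them, and the promised comparison is routed through the Hackney reference.

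**Conclusion.** The point holds as a fault in the stated comparator rule. The Newham increment can reflect only borough differences. The Tower Hamlets increment departs from the counterfactual used for its own effectiveness result. No borough adjustment is described for this step.

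Neither direction nor size can be established from the article. The 17% and 20% figures illustrate the scale under equal uptake and positivity proportional to diagnosed prevalence. Over the assumed uptake range the artefact runs from about −59% to +24% for Newham and −60% to +20% for Tower Hamlets. These are ratios of diagnoses, not of cost per quality-adjusted life year. Confidence is high in the mismatch of comparators and low in any particular bias.

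**What to change.** Reword the second economic analysis as follows:

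1. Take each active borough's effect from the planned ITS analyses: its change from its own pre-intervention counterfactual, net of the Newham trend.
2. Make usual care the common reference, with zero effect by definition.
3. Apply the effects to one model population with a common baseline testing rate and prevalence, and show borough-specific prevalence as a scenario.
4. Keep the never-trained Hackney practices as comparator for the within-Hackney analysis only.

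Replacing the Hackney reference with Newham while still comparing levels would not be enough.

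The cost is a change of wording, since both ITS analyses with Newham as comparator are already planned. The downside is reliance on Newham as a parallel trend. Some Newham practices ran rapid-testing pilots that may not be accounted for, and its data are extracted differently from Hackney's. The article acknowledges both. A constant difference in extraction would cancel in each borough's own change, but one that shifts over time would not.

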## Ethical aspects

The programme described is an evaluation of routine care. Its status as such has been endorsed by the chair of the Camden and Islington NHS Research Ethics Committee London. The committee’s view is that the work does not require NHS ethics approval. The programme will be implemented in partnership with the local providers and commissioners and involve the analysis of existing routine data. This also applies to data on delayed diagnosis of HIV (CD4 count), and demographics reported in the RHIVA2 trial, which is routinely collected as part of a national audit (BHIVA National Audit 2010) and has been included in Public Health Outcomes Framework (http://www.phoutcomes.info). We will inform the research ethics committee, the CCG and Public Health about any important changes to the protocol.

This service evaluation is to answer the question: what standard does this service achieve? It involves routine implementation of an intervention outside of the research context. The actual management options are those of the clinician and patient only. There is no random allocation to intervention and control groups. No individual consent is required from newly diagnosed patients.

In addition to CD4 count and viral load, the following additional data will be obtained by the clinical leads of specialist departments in an anonymised fashion and stored in accordance with good clinical practice:Most likely mode of HIV acquisitionSexual orientationSoundex codeEthnicityGenderAge at diagnosis.

## Discussion

The MRC Framework for complex interventions^28^ clearly describes the need for implementation studies that test the effectiveness of interventions found to be promising in phase III randomised controlled trials. Successful translation of such interventions into routine care cannot be assumed; trials take place in tightly controlled conditions that aim to limit bias, with selected (often motivated) participants, while implementation programmes (usually) aim much more broadly to include all potential participants.^29^ Trial interventions will often need to be augmented by a distinct implementation package. Their success will be affected by multiple factors including, but not limited to contextual factors such as, differences in setting, population, organisation of healthcare systems, competing initiatives and financial aspects (including availability of incentives). Evaluations of implementation of trials into routine care are frequently not carried out, and if they are, are often poorly reported.^30^ Such evaluations are highly unlikely to involve randomised designs, and are more likely to be observational, including the use of service evaluations. Designs are often constrained by health systems and data availability, but need to be as robust as possible. New reporting guidelines have recently been published that highlight the need for evaluation of implementation and aim to improve their reporting, such that they can be more easily accessed in the literature and serve to guide others in designing the most effective implementation programmes.^29^

Recent NICE guidelines recommend expanded HIV testing in primary care,^6–8^ but little information is available about how to operationalise testing, especially in the context of current resource constraints in primary care. It is, therefore, vital that innovative and effective ways are found to implement testing. The strengths of the proposed work include the availability of existing trial data preceding the implementation programme, the capacity to collect data longitudinally using similar methods to those used in the trial, and the use by general practices across all three participating boroughs of a single GP computer system supplier Egton Medical Information Systems, data from which can be remotely and electronically (with full anonymisation) searched and collated by the research team (http://www.blizard.qmul.ac.uk/ceg-home.html), confirmation of HIV test results for all study practices at the same tertiary care laboratory (Barts Health NHS Trust) and external data validation by Public Health England. This approach provides a unique capability, allowing comparative data on three separate approaches to HIV testing and diagnosis to be accurately gathered and analysed.

Due to difference in data extraction between Hackney and Tower Hamlets and Newham, respectively, there may be a small chance of differential reporting bias between these boroughs. In contrast to the Department of Sexual Health at Homerton University Hospital (Hackney), which is able to track any patient lost to follow up using a monthly list of HIV positives provided by the laboratory, no such fail-safe procedure exists in Tower Hamlets or Newham. However, in these latter boroughs all data for HIV positive test results are available on the general practice computer system via an electronic laboratory link, almost eliminating the chance of missing data. We are currently conducting an audit of outcomes from people newly diagnosed with HIV in Tower Hamlets and Newham general practices to extract this data for the study period specified.

We cannot exclude occurrence of any cluster or crossover effects, although we would expect for this to be minimal given that we detected a more than fourfold increase in HIV testing rates between the RHIVA2 trial intervention and control practices. In contrast to the network structure in Tower Hamlets, Hackney practices, which were randomly allocated to the trial arms, may have informally worked collaboratively through geographical proximity. Due to this potential clustering effect, inference of generalisability of RHIVA2 findings in other boroughs should, therefore, be treated with caution. Furthermore, an audit of new diagnosis and safe coprescribing was also conducted by our team across 31 of the 44 Hackney practices during the implementation phase‚ potentially causing contamination of control practices. However, the number of both trial intervention (n=13) and control (n=15) practices was comparable, suggesting equal exposure to this audit across both arms.^22^ Although public health teams informally collaborate across Northeast London, crossover between boroughs is unlikely given that services are developed and budgeted separately. Our analysis will adjust for any potential contamination using various vertical and horizontal controls both within Hackney, as well as between boroughs using Newham, which has been devoid of any local service HIV promotional intervention, as control.

Moreover, the RHIVA2 trial and post-trial implementation will not be grouped as the same intervention. We will only use the post-trial implementation practices in the main analysis and only consider the trial intervention practices for the assessment of sustainability. Therefore, the sustainability analysis will have to be interpreted with caution with regards to the sustainability of the post-trial intervention, as the intervention in trial conditions might be different to that outside of trial conditions.

We may not be able to account for missing data such as from patients lost to follow-up after diagnosis in general practice, or from rapid testing pilots conducted in a small number of Newham practices during the study period.

Finally, the RHIVA2 trial intervention was adapted for the implementation phase (1) to expand promotion of routine offer of HIV testing from new registration checks to include sexual health and contraception appointments and (2) to enhance screening through additional use of venous blood sampling. This protocol adaptation was made to meet the needs of the local population through increasing access to testing, reflecting the complexities of translating a research intervention into clinical practice after completion of the research.

The results of the proposed analysis are likely to be of considerable interest to commissioners, particularly given that late diagnosis of HIV is a UK Public Health Outcomes Framework priority,^31^ and that cost-effectiveness of HIV testing is complex, and becoming cost-effective in trial-based models only after a period of time has elapsed to counter the additional significant costs of early treatment.
